**Table 1 T1:**
[figure not shown]
Schedule of enrolment, interventions, and assessments of treatments.

The participants will be randomized into 2 groups: intervention group [analgesia with LED therapy (n = 30)] and control group [analgesia with bath therapy (n = 30)]. The perception of pain will be evaluated using the visual analogue scale (VAS) with a score from 0 to 10 at baseline, that is, before the intervention. In both the groups, the procedure will last 10 minutes at each of 3 time points during labor: cervical dilation of 4 to 5 cm, 6 to 7 cm, and 8 to 9 cm.^[33]^ At the 3 time points, the level of pain will be assessed using VAS shortly after the intervention. Pharmacological analgesia will be promptly performed whenever necessary; in these cases, the participant will be excluded from the study and replaced with another consecutive participant.

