### Objectives of the study

2.2

Primary objective: To evaluate the effect of LED photobiomodulation on analgesia during labor as an alternative nonpharmacological intervention.

Research hypotheses:

Hypothesis 0 (null): the use of LED photobiomodulation exerts an analgesic effect similar to that of the bath therapy.

Hypothesis 1: the use of LED photobiomodulation exerts an analgesic effect superior to that of the bath therapy.

Hypothesis 2: the use of LED photobiomodulation exerts an analgesic effect inferior to that of the bath therapy.

Secondary objective: To evaluate fetal conditions using cardiotocography and the Apgar score in the first and fifth minutes after birth, and the level of satisfaction with the experience of childbirth using a questionnaire.

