### Participants

2.3

The study participants will be women aged >18 years, who are expected go into natural labor in the Maternity Hospital of Mandaqui. The inclusion criteria for the study will be as follows: women who request analgesia during labor; nulliparous and multiparous women; women with term gestation; women without previous diseases, including diabetes, neurological diseases, and metabolic diseases; and women in whom it is possible to evaluate fetal vitality during analgesia.

The exclusion criteria will be as follows: women whose labor is induced with medications; women who request drug analgesia during labor; and women who undergo cesarean delivery.

The participants will be recruited on admission at the maternity hospital and will be randomized in the 2 study groups after clarifying regarding the study objectives and obtaining their informed consent.

The sample size has been estimated using the difference in means in the score of the VAS from a study that evaluated analgesia during labor.^[34]^ The difference in the mean VAS score between the groups was set as 2 (standard deviation: 1.6). The minimum number of participants considering a power of 80% and level of significance of 5% was 28, and the minimum number of participants per group considering possible exclusions was 30.

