### Randomization

2.4

The patients will be distributed into the 2 groups by performing block randomization (n = 6) at a ratio of 1:1 according to a code generated by the SPSS software version 20.0 for Windows (IBM Corporation, Armonk, NY).

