### Data analysis

2.7

The distribution of the VAS scores will be analyzed, and the continuous variables with normal data distribution will be compared using the *t* test and expressed as mean ± standard deviation. The categorical variables will be analyzed using the *χ*^2^ test or Fisher exact test. Non-normal data will be analyzed using the Mann–Whitney *U* test. All analyses will be performed using the statistical software SPSS version 20.0 for Windows (IBM Corporation, USA) at a level of significance of 5%.

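### The stated minimum of 28 for 80% power does not follow from a difference of 2 and SD of 1.6: a two-sided t test needs 12 per group

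*Protocol article*

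**What the plan says.** Section 2.3 (Participants) takes its planning values from a cited study of analgesia in labor: "The difference in the mean VAS score between the groups was set as 2 (standard deviation: 1.6"). It then states the result, "The minimum number of participants considering a power of 80% and level of significance of 5% was 28", and continues that "the minimum number of participants per group considering possible exclusions was 30". The 28 carries no unit. Neither the test behind the calculation nor its sidedness is given, and no exclusion rate is stated.

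Other sections fix the remaining inputs. Section 2.4 (Randomization) plans "block randomization (n = 6) at a ratio of 1:1". Section 2.2 (Objectives of the study) has hypotheses in both directions, including "Hypothesis 2: the use of LED photobiomodulation exerts an analgesic effect inferior to that of the bath therapy". Section 2.7 (Data analysis) says that "continuous variables with normal data distribution will be compared using the *t* test", and that "Non-normal data will be analyzed using the Mann–Whitney *U* test", at the 5% level.

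**The concern.** The standardised difference is 2/1.6 = 1.25, which is large. An effect of that size needs only about a dozen women per arm, so 28 looks too high for 80% power.

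The power statement tells the reader what effect the trial was built to detect. If 28 per group really was the 80% figure, the calculation used a larger SD or a smaller difference than the article reports, and the true design target is not the printed one. If 2 and 1.6 are right, the power is far above 80%, and the trial has good power for differences well below 2 points. As written, the reader cannot tell which case applies.

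**Working it through.** **Inputs.** Difference 2, SD 1.6, power 80%, significance level 5% (section 2.3); 1:1 allocation (section 2.4). Two-sided testing is an assumption, taken from the two-directional hypotheses in section 2.2. The t test is the first-named test in section 2.7 and fits planning values given as a mean difference and an SD.

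**Attempt to reproduce 28 with the t test.**

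- Normal approximation: n per group = 2(z₀.₉₇₅ + z₀.₈₀)²/d² = 2(1.960 + 0.842)²/1.25² = 10.05, so 11 per group, 22 in total.
- Noncentral t, with noncentrality d√(n/2) and 2n − 2 degrees of freedom: 11 per group gives 79.6% and 12 per group gives 83.3%. The requirement is 12 per group, 24 in total.
- One-sided, the requirement falls to 9 per group (8 by the normal approximation), further from 28.

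**Power at the stated numbers (two-sided t test, d = 1.25).**

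| Reading | n per group | Noncentrality | Power |
|---|---|---|---|
| 28 in total | 14 | 3.31 | 88.9% |
| 28 per group | 28 | 4.68 | 99.6% |
| Planned size | 30 | 4.84 | 99.7% |

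**What 28 per group at 80% power would imply.** The standardised difference would have to be 0.762. That is an SD of 2/0.762 = 2.62 at a difference of 2, or a difference of 0.762 × 1.6 = 1.22 at SD 1.6. At 30 per group the standardised difference detectable with 80% power is 0.736, which is 0.736 × 1.6 = 1.18 points at SD 1.6.

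**Other routes to a per-group 28.** One-sided testing, 90% or 95% power, Mann–Whitney efficiency adjustments, Bonferroni over three time points, and an SD inflated by √2 were all tried. None gives 28 per group; the largest result is 22, from the inflated SD.

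**Routes to a total of 28.**

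- Noether's formula for the Mann–Whitney test: p = Φ(1.25/√2) = 0.812, and N = (1.960 + 0.842)²/[3 × (0.812 − 0.5)²] = 26.9. That becomes 28 in two equal groups.
- Bonferroni over the three dilation time points, normal approximation: 2(2.394 + 0.842)²/1.5625 = 13.4, so 14 per group. The noncentral t version needs 15.

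Section 2.3 mentions neither method. Simulated Mann–Whitney power for normal data is about 80% at 12 per group (79.8%), 83% at 13 and 86% at 14, so even for that test 28 in total is somewhat more than 80% power requires.

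**The step to 30.** From 28 to 30 per group leaves room for 2/30 = 6.7% losses, a plausible allowance. From 28 in total to 60 in total would more than double the sample in the name of exclusions.

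**The case against.** The strongest defence is that section 2.3 names no test and no unit, and that section 2.7 plans the Mann–Whitney test as well as the t test. Read as a total, 28 can be obtained from the stated inputs by Noether's formula, or by a Bonferroni correction with the normal approximation. This stands to the following extent: a reader might infer that 28 is wrong however it is read, and the documents do not support that. The defence does not rescue the text as written, because it needs a method that the text does not state and it leaves the rise to 30 per group unexplained.

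A reader might also infer that exclusions are counted twice, since women given pharmacological analgesia are replaced (section 2.1: "the participant will be excluded from the study and replaced with another consecutive participant") and section 2.3 adds an allowance as well. That inference fails. The replacement rule is stated for those women only. Section 2.3 also excludes women who undergo cesarean delivery, and no replacement is stated for them. Women are recruited on admission, so a cesarean can follow randomization. The allowance can cover such losses without overlapping the replacement rule.

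Third, the error runs in the safe direction: with the stated inputs, t-test power for 2 points is above 80% on either reading. This stands and lowers the severity. Finally, a condensed article may leave the test and sidedness to a fuller document. That excuses the omissions, but not a printed number that disagrees with the inputs printed beside it.

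**Conclusion.** The point holds in a limited form. On the per-group reading that the text itself implies, 28 is about 2.3 times the 12 per group that the stated inputs require (28/12), and its power is 99.6% rather than 80%. On the total reading, t-test power is 88.9%, and 28 is reached at 80% only through an unstated method. The calculation is therefore not reproducible as written: either the difference or the SD is misreported, or the power figure is wrong. The documents do not show which, because the cited study is not at hand.

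This rests on a two-sided 5% test, equal groups and a common SD of 1.6. Nothing here shows that the trial is too small. If 2 and 1.6 are right, the planned 30 per group has 99.7% power for 2 points. Severity is moderate.

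**What to change.** Check the difference and the SD against the calculation actually run, then restate the paragraph in section 2.3. Say whether each figure is per group or in total, and which test and sidedness were used.

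- If 2 and 1.6 are right, write: at two-sided 5% and SD 1.6, a two-sample t test needs 12 per group for 80% power to detect 2 points; the planned 30 per group gives more than 99% power for 2 points and 80% power for about 1.2 points.
- If another SD or difference was used, correct the printed value and keep the rest consistent with it.
- If 28 was a total from a Mann–Whitney or multiplicity-adjusted calculation, name the method and explain separately why 30 per group was chosen.

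The cost is one paragraph. Enrolment stays at 30 per group, and this point calls for no change to the exclusion allowance or the replacement rule.

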### Randomization

2.4

The patients will be distributed into the 2 groups by performing block randomization (n = 6) at a ratio of 1:1 according to a code generated by the SPSS software version 20.0 for Windows (IBM Corporation, Armonk, NY).

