### Study design

2.1

This randomized controlled trial will be conducted at the maternity ward of a public hospital in São Paulo, state of São Paulo, Brazil. In total, 60 uniparous or multiparous women who request analgesia during labor will participate in the study.

This study complies with the ethical guidelines in human research and was approved by the Research Ethics Committee of the Mandaqui Hospital (São Paulo, Brazil) under Opinion number 2.47.650 and has been registered in Clinical Trials under Protocol No NCT03496857. This is a randomized controlled clinical study; for the purpose of greater transparency and quality of the research, Table 1 summarizes the enrollment, intervention, and assessment schedule, all of which are in accordance with the SPIRIT (Standard Protocol Items: Recommendations for Interventional Trials) recommendations.

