#### Intervention group: LED therapy

2.5.1

LED therapy sessions will be held in the prelabor room. The patient who will undergo analgesia and the professional responsible for placing the LED plate on the patient's back, between T10 and L2, will be present at the time of the intervention. The LED plate will be covered with clear disposable polyvinyl chloride to avoid cross-contamination and ensure hygiene. During the interventions, the patient will be allowed to choose the position that is the most comfortable for her.

Three 10-minute LED applications will be performed when the patient has a cervical dilatation of 4–5, 6–7, and 8–9 cm. Data on the level of pain, characteristics of the membrane (intact or damaged), heart rate, cardiotocography, and uterine dynamics will be collected after each intervention.

The LED device used is SportLux (Cosmedical, São Paulo, Brazil), and the dose parameters are shown in Table 2.

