### Control group: bath therapy

2.6

The method of analgesia with the bath therapy will be performed using a hot shower at 37°C for 10 minutes. After showering the entire body or the back for 5 minutes, the participants will be allowed to direct the water flow to any area of the body that feels the most comfortable and to adjust the temperature themselves for improved comfort. Bath therapy will be performed at 3 time points during labor: at cervical dilatation of 4–5 cm, 6–7 cm, and 8–9 cm. Data on the level of pain, membrane characteristics (intact or damaged), heart rate, cardiotocography, and uterine dynamics will be collected after the bath therapy by performing the same measurements used in the intervention group.

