## Discussion

3

This study describes the protocol for a randomized controlled clinical trial aimed to evaluate the effect of LED therapy on analgesia during labor. The advantages of using LED therapy for analgesia during labor include the ease of application, the feasibility of application by the same team that assists the patient during labor, the possibility of the patient choosing the position that feels the most comfortable, even under analgesia, and improved mobility; the patient can remain in the upright position to help the fetal descent.

The main contribution of this clinical trial is the development of an analgesic intervention during labor that is effective and accessible for use in various public and private health services. The findings of this study may help develop protocols for analgesia during labor, thus allowing patients to not be afraid of pain and promote vaginal delivery.

This study will be the first to use photobiomodulation for analgesia during labor, and the results may help elucidate the correlation between phototherapy in pregnant women and fetal characteristics during therapy. In case of favorable outcomes, this approach can be used as a noninvasive and nonpharmacological alternative for analgesia during labor.

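### A single fixed block size of 6, in one ward with treatments staff cannot be masked to, makes about a quarter of allocations knowable in advance

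*Protocol article*

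**What the plan says.** - **Sequence.** Section 2.4 (Randomization) specifies "block randomization (n = 6) at a ratio of 1:1", "according to a code generated by the SPSS software version 20.0 for Windows". One size is given. Neither variation in size nor stratification is mentioned, so the text describes one list of blocks of six.
- **Setting and size.** Section 2.1 (Study design) says the trial "will be conducted at the maternity ward of a public hospital in São Paulo", with 60 women, 30 per arm.
- **Treatments.** In section 2.5.1, "the professional responsible for placing the LED plate on the patient's back, between T10 and L2, will be present" during the LED session. In section 2.6 the control treatment is "performed using a hot shower at 37°C for 10 minutes". The article does not use the term open-label, but it describes no blinding, and the people giving care could not mistake one treatment for the other.
- **Entry.** Section 2.3 (Participants) has women recruited on admission and randomized after consent.
- **Outcome.** Pain is self-rated on a 0 to 10 VAS at baseline and after each of three sessions (section 2.1).

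**The concern.** A 1:1 block of six must end with three women in each arm. Once three in a block have gone to one arm, the rest of that block is fixed. Hiding the list, for instance in sealed envelopes, does not prevent this: the block size and the visible past allocations are enough.

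A recruiter with that knowledge could approach, delay or pass over a woman according to the arm she is about to get. The entry criteria leave some room for judgement, such as whether she is requesting analgesia and whether fetal vitality can be evaluated. The outcome is subjective, and the article states its expectation that LED will prove superior. If women expected to cope better were steered towards one arm, part of the VAS difference would reflect who was enrolled and not the treatment.

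**Working it through.** The article gives no figure for predictability, so there is none to reproduce. Inputs: block size 6 and ratio 1:1 (section 2.4); 60 women (section 2.1), hence 60 / 6 = 10 blocks; SD 1.6 and planned difference 2 (section 2.3), used only in step 5.

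**1. Allocations known with certainty.** These are the final run of same-arm allocations in a block. The last is always certain. The last two match with probability 2/5 = 0.40. The last three match with probability 0.40 × 1/4 = 0.10. Four cannot match.

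- Expected number per block = 1 + 0.40 + 0.10 = 1.5.
- Share = 1.5 / 6 = 25%.
- Over 10 blocks: 15 of 60 on average, and at least 10.

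Enumerating all 20 possible sequences gives the same result: exactly 1, 2 or 3 certain allocations with probability 0.60, 0.30 and 0.10.

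**2. Best guess for every allocation.** The strategy is to guess the arm that is behind and toss a coin when the arms are level. For a block of size b, the expected number correct = b/2 + 2^(b−1)/C(b, b/2) − 1/2. With b = 6: 3 + 32/20 − 0.5 = 4.1, and 4.1 / 6 = 68.3%, against 50% by chance.

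**3. The other reading of the notation.** If n = 6 meant six blocks of 10, 16.7% would be certain (10 of 60) and 65.3% guessed correctly. The mechanism is the same but weaker.

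**4. Varying the block size.** This was simulated over 60 allocations, with an optimal guesser who knows the possible sizes but not their order.

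| Block sizes | Certain | Best guess correct |
|---|---|---|
| 6 only | 25% | 68.3% |
| 4 and 6 | 5.5% | 69.0% |
| 4, 6 and 8 | 2.3% | 67.8% |

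With 4, 6 and 8, 0.023 × 60 = about 1.4 allocations are certain. The guess rate hardly moves because guessing the arm that is behind needs only the running totals, not the block size.

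**5. What steering could do (assumed shifts, for scale only).** Suppose every certain place is used, and the women placed there differ by s VAS points in the favourable direction in each arm. The bias is 0.25s + 0.25s = 0.5s. The standard error with 30 per arm is 1.6 × √(2/30) = 0.41.

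| s (assumed) | Bias in VAS points | Two-sided type I error |
|---|---|---|
| 0 | 0 | 5% |
| 0.5 | 0.25 | about 9% |
| 1.0 | 0.50 | about 23% |

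A bias of 0.50 is a quarter of the planned difference of 2. With sizes 4, 6 and 8 and s = 1, the part due to certain places falls to 2 × 0.023 = about 0.05 points.

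**The case against.** The strongest reply is that the harm needs three things together: a recruiter who knows the block size, who has followed every past allocation, and who controls who is approached. The article establishes none of these. It does not say who recruits, who holds the code or how assignments are released, and an article commonly leaves such details to the full protocol. This stands: selective enrolment is a risk here, and missing concealment details are not part of the point.

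Several stronger readings are tempting, and the text does not support them.

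- *The treating team chooses who enters.* The Discussion mentions "the feasibility of application by the same team that assists the patient during labor", but as a general advantage of LED therapy. It concerns giving the treatment, not enrolment.
- *A replacement's arm is known beforehand.* Section 2.1 says an excluded woman is "replaced with another consecutive participant". It does not say that the new woman takes the vacated arm; the next position on the list fits the wording at least as well.
- *No analysis could repair the bias.* Baseline VAS is collected, so imbalance in pain at entry can be seen and adjusted for. What adjustment would miss is selection on features that the baseline score does not capture, such as expected tolerance or progress of labor.
- *The 68% guess rate is the price of the fixed size.* It belongs to small permuted blocks in general and stays near 68% when the sizes vary.

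What the reply does not remove is the 25%. That follows from a choice the article states, and concealing the list would not change it.

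**Conclusion.** The point holds as a design weakness with a cheap remedy. It is neither a contradiction in the article nor evidence that enrolment was steered. Anyone who recruits, knows the block size and sees past allocations can know on average 25% of them in advance: about 15 of 60, including at least the last of each block.

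This assumes that n = 6 is the block size, that there is one unstratified list, and that 60 allocations are made in complete blocks. If replacements take further list positions, the 25% share is unchanged and the count rises in proportion. The size of any bias is unknown; the figures in step 5 of the working depend on assumed shifts. Adjustment for baseline VAS would recover part of it, not all.

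**What to change.** Generate the list, or its remaining part from the end of the current block, with block sizes drawn at random (for example 4, 6 and 8), and do not disclose the sizes to those who recruit.

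- **Gain.** Certain allocations fall from 25% to about 2%, even for someone who knows which sizes are possible. Best-guess accuracy stays near 68%, so the change removes certain foreknowledge but not better-than-chance guessing.
- **Cost.** One new list. If enrolment stops inside a block of 8, the arms differ by at most 4 women, for example 32 against 28. The standard error then changes by a factor of √[(1/32 + 1/28) / (2/30)] = 1.002, a negligible loss of power.

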### Procedures

2.5

#### Intervention group: LED therapy

2.5.1

LED therapy sessions will be held in the prelabor room. The patient who will undergo analgesia and the professional responsible for placing the LED plate on the patient's back, between T10 and L2, will be present at the time of the intervention. The LED plate will be covered with clear disposable polyvinyl chloride to avoid cross-contamination and ensure hygiene. During the interventions, the patient will be allowed to choose the position that is the most comfortable for her.

Three 10-minute LED applications will be performed when the patient has a cervical dilatation of 4–5, 6–7, and 8–9 cm. Data on the level of pain, characteristics of the membrane (intact or damaged), heart rate, cardiotocography, and uterine dynamics will be collected after each intervention.

The LED device used is SportLux (Cosmedical, São Paulo, Brazil), and the dose parameters are shown in Table 2.

